#### Economic evaluation

##### Cost-effectiveness of the intervention

We will conduct an economic evaluation from a societal perspective in accordance with the Dutch guidelines for economic evaluation [50]. Effectiveness is presented in terms of quality-adjusted life years (QALYs). QALYs are a combination of quality of life and survival, where quality of life is expressed as a utility score between 0 (representing death) and 1 (representing perfect health). Utility scores will be calculated through the SF-6D, which is a well-known classification for describing health derived from a selection of SF-36 items [36, 51]. Based on the SF-6D health state, each patient is assigned a utility score at three time points (baseline, 4 months, 12 months), using tariffs from the general population. QALYs will be calculated using the area-under-the-curve method, using the utility scores at baseline, 4 months and 12 months.

Since the economic evaluation will be performed over a time horizon of 1 year, costs and effects will not be discounted.

The cost analysis consists of two main parts. First, at patient level, volumes of care related to the care of patients with MUS will be measured by means of the iMCQ and iPCQ [41, 42]. The second part of the cost analysis consists of determining the cost prices for each volume of consumption. The standard cost prices from the ‘Dutch Guidelines for Cost Analyses’ [52] will be used to determine the cost prices for each volume of consumption. For units of care where no standard prices are available real cost prices will be determined. To obtain total costs, resource use will be multiplied with the cost prices. Productivity losses will be valued by means of the friction cost method [53–55].

Differences in costs and QALYs per patient between the two treatment arms will be calculated, according to the ITT and the per-protocol principle. Patients in the intervention group that have completed at least four sessions will be used for the per-protocol analysis. Where relevant, incremental cost-effectiveness ratios (ICERs) will be calculated to reflect the extra costs per QALY gained.

Uncertainty in the ICER will be presented non-parametrically using bootstrap techniques [56]. The bootstrap replications will be used to estimate 95% confidence intervals around cost and QALY differences. Results will be graphically presented and analysed by means of a cost-effectiveness plane and cost-effectiveness acceptability curves [57]. A secondary analyses will be performed from a health care perspective.

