**Methods:**

A randomised effectiveness trial with an economic evaluation in primary care with 158 patients aged 18 years and older who are frequently consulting their GP with MUS. Patients will be assigned to psychosomatic therapy in addition to usual care or usual care only. Psychosomatic therapy is a multi-component and tailored intervention, aiming to empower patients by applying psycho-education, relaxation techniques, mindfulness, cognitive approaches and/or graded activity. Patients assigned to the psychosomatic therapy receive 6 to 12 sessions of psychosomatic therapy, of 30–45 min each, delivered by a specialised exercise or physical therapist.

Primary outcome measure is patient-specific functioning and disability, measured with the Patient-Specific Functional Scale (PSFS). Secondary outcome measures are symptom severity, consultation frequency and referrals to secondary care, patient satisfaction, quality of life and costs. Assessments will be carried out at baseline, and after 4 and 12 months.

An economic evaluation alongside the trial will be conducted from a societal perspective, with quality-adjusted life years (QALYs) as outcome measure. Furthermore, a mixed-methods process evaluation will be conducted.

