**Fig. 1 Fig1:**
[figure not shown]
Schedule of enrolment, interventions and assessments. *PST* psychosomatic therapy; *CAU* care as usual; *PHQ-15* Patient Health Questionnaire 15-item somatic symptom scale; *PSFS* Patient Specific Functioning Scale; *iMCQ* iMTA Medical Consumption Questionnaire; *iPCQ* iMTA Productivity Cost Questionnaire; *NRS* numeric rating scale; *SF-36* Short Form Health Survey-36 items; *4DSQ* Four Dimensional Symptom Questionnaire; *GPE* Global Perceived Effect; *IAS* Illness Attitude Scale; *IPQ-B* Brief Illness Perception Questionnaire; *SRS-DV* Session Rating Scale Dutch version; *WAI-SF* Working Alliance Inventory short form; *1* only intervention group, directly after first session; *2* only intervention group directly after last session

We will perform a pragmatic randomised effectiveness trial with economic evaluation in primary care with patients aged 18–80 years who frequently, i.e. twice or more in the past months, consult their GP for MUS. Details regarding recruitment are presented below (see ‘Recruitment of study participants’ section). Patients will be individually randomised into intervention (psychosomatic therapy in addition to usual care) or control condition (usual care alone). The intervention (psychosomatic therapy) consists of 6 to 12 sessions, depending on number and severity of the patient’s symptoms, each of 30–45 min. Therapy will be delivered by a qualified psychosomatic therapist. The primary outcome measure will be functioning and disability measured with the Patient-Specific Functional Scale (PSFS) [24]. All patients will be followed for 1 year and will be asked to complete questionnaires at baseline and at 4 and 12 months’ follow-up. Participants in the intervention group will be referred to one of the 26 participating qualified psychosomatic therapists, physiotherapists or exercise therapists with a special interest in MUS, who receive a training for this study.

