Illness beliefs are measured with the brief Illness Perception Questionnaire (IPQ-B) [39]. A higher score reflects a more threatening view of the illness. The IPQ-B is based on the revised IPQ-R [40] and designed to assess the cognitive and emotional representations of illness. It consists of nine items in total. Six items assess cognitive illness representations: consequences, timeline, personal control, treatment control, identity and comprehension of illness. One item reflects emotional representation, one item assesses a combination of emotional and cognitive representation: concern. The score will be rated on an 11-point scale, ranging from 0 (not at all) to 10 (very much). The last item is an open-question to assess causal representation.

The GP will be asked to report the total number of consultations of the patient in the year after the psychosomatic therapy.

All other medical consumption will be measured with the iMTA Medical Consumption Questionnaire (iMCQ) [41]. This questionnaire measures all relevant health care-related costs like outpatient visits at any medical specialist, hospitalisations and imaging procedures.

Productivity losses due to illness or recovery will be estimated based on patient-reported absences from paid labor measured with the iMTA Productivity Cost Questionnaire (iPCQ) [41, 42]. For all secondary outcome measures we will measure mean change from baseline at 4 and 12 months’ follow-up.

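### The 12-month cost difference is bootstrapped with no baseline-cost term, although baseline costs appear to be collected: precision is given up, but the estimate remains valid

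*Protocol article*

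**What the plan says.** The section on cost-effectiveness of the intervention (Economic evaluation) builds the cost result in steps. First, "volumes of care related to the care of patients with MUS will be measured by means of the iMCQ and iPCQ". Resource use is then multiplied by unit prices to give total costs over a one-year horizon. After that: "Differences in costs and QALYs per patient between the two treatment arms will be calculated, according to the ITT and the per-protocol principle". For uncertainty, "The bootstrap replications will be used to estimate 95% confidence intervals around cost and QALY differences", and the results also go into a cost-effectiveness plane and acceptability curves. No regression or baseline cost is named in this sequence. Baseline is mentioned there only for the utilities that enter the QALY area under the curve.

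Three other places bear on the point:

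- Study design gives the general timetable: "All patients will be followed for 1 year and will be asked to complete questionnaires at baseline and at 4 and 12 months’ follow-up".
- Secondary outcomes, directly after describing the iMCQ and iPCQ, says: "For all secondary outcome measures we will measure mean change from baseline at 4 and 12 months’ follow-up".
- The abstract counts costs as a secondary outcome: "Secondary outcome measures are symptom severity, consultation frequency and referrals to secondary care, patient satisfaction, quality of life and costs". The effect evaluation assigns secondary outcomes to a random-intercept mixed model that uses the baseline, 4-month and 12-month measurements.

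**The concern.** The cost difference is the numerator of the ICER and, with the QALY difference, determines the acceptability curve. Lower cost is also part of the main aim given under sample size and power calculation, although the trial is sized on the PSFS and not on costs. If a pre-randomisation cost is on file for each patient and predicts later cost, an unadjusted difference leaves explainable variation in the result. Chance differences between the arms in prior cost then add noise to the incremental cost, and its interval is wider than it needs to be.

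The mixed model does not clearly close the gap. It appears under the effect evaluation and compares change scores, whereas the ICER needs a total cost over the year, obtained under a separate heading by a separate bootstrap. The article does not say how the two relate.

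**Working it through.** **1. The plan's own figure.** Inputs from sample size and power calculation: difference 1, SD 2, alpha 0.05 (two-sided assumed), power 0.80, dropout 20%.

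- n per arm = 2 × (1.960 + 0.842)² × 2² / 1² = 62.8, so 63 evaluable.
- 63 / 0.80 = 78.75, so 79 per arm and 158 in total.

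This agrees with the protocol. I use 63 per arm as the number with cost data, which is an assumption. The ratios below hardly depend on it.

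**2. Unadjusted cost difference, in units of the cost SD.** The protocol gives no cost SD, so everything is relative to it.

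- SE = √(2/63) = 0.178 SD.

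**3. Adjusted for baseline cost as a covariate.** With rho the correlation between baseline and follow-up cost, SE(adjusted) ≈ √(1 − rho²) × 0.178. Rho is not in the documents and is varied as an assumption. For comparison, a simple change score (equal SDs at both times) has SE ratio √(2(1 − rho)). The chance baseline difference carried into the unadjusted contrast has mean absolute size rho × 0.178 × √(2/π).

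| rho (assumed) | SE adjusted (SD) | Ratio to unadjusted | Interval narrower by | Change-score ratio | Mean carry-over (SD) |
|---|---|---|---|---|---|
| 0.2 | 0.175 | 0.980 | 2% | 1.26 | 0.03 |
| 0.3 | 0.170 | 0.954 | 5% | 1.18 | 0.04 |
| 0.5 | 0.154 | 0.866 | 13% | 1.00 | 0.07 |
| 0.7 | 0.127 | 0.714 | 29% | 0.77 | 0.10 |

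Below rho 0.5 a change score is worse than no adjustment, so the form of the adjustment matters.

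**4. Check with skewed costs.** The formulas do not allow for the skewness usual in costs. A simulation used lognormal costs, 63 per arm, 6,000 replicates and no true effect. The adjusted-to-unadjusted SD ratios were 0.98, 0.95, 0.86 and 0.66 at rho 0.2, 0.3, 0.5 and 0.7. Both estimators were centred on zero (mean error at most 0.003 against an unadjusted SD of about 0.38). The gain is therefore in precision only.

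**5. Limit of these figures.** They concern the cost difference alone. How far the acceptability curve sharpens also depends on QALY variation and the cost–QALY correlation, neither of which is given.

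**The case against.** The strongest reply is that the economic section never calls the difference unadjusted. A baseline-adjusted difference, refitted in each replicate, would fit the same sentences, and a journal article may leave covariates to a fuller plan. Costs are also classed as a secondary outcome, and secondary outcomes go to a model that uses baseline. This stands to the extent that non-use of baseline cost is inferred and not declared. It does not remove the point. The section spells out the cost calculation from volumes to bootstrap with no baseline term, and nothing says that the mixed model supplies the ICER numerator. If its change-score framing were carried over as a simple change score, precision could fall.

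Baseline collection is also an inference. It rests on the sentence about change from baseline and the general timetable, because the schedule figure is not shown.

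The predictive value of baseline cost is uncertain too. Patients are selected on GP attendance, but GP consultations are reported by the GP for the year after therapy, and the iMCQ covers other consumption. Selection on GP visits therefore does not show that baseline iMCQ/iPCQ cost has a high rho.

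A reader might infer that chance baseline differences bias the cost result or make its interval too narrow. The documents do not support that: allocation is random and the bootstrap interval already allows for chance imbalance. A reader might also infer a loss of power for costs. The trial is not sized on costs and the economic section plans estimation with no stated cost test, so any power figure would start from an arbitrary base.

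**Conclusion.** The point holds as an avoidable loss of precision and an unstated link between two analyses. As written, the 12-month cost difference and its bootstrap use no baseline-cost term, and their relation to the mixed model is left open. The planned difference is unbiased with a valid interval. The likely gain runs from negligible (2% at rho 0.2) to material (29% at rho 0.7). It rests on an assumed rho and on the iMCQ and iPCQ being completed at baseline. The change is worth making because it is nearly free and concerns a headline result. The data analysts will also know the allocation (allocation and blinding), so fixing the covariate beforehand removes a later choice over the ICER.

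**What to change.** In the section on cost-effectiveness of the intervention, state that the incremental cost is estimated by regressing each patient's 12-month total cost on arm and baseline iMCQ/iPCQ cost. For the health care perspective, use baseline health care cost. Enter baseline cost as a covariate and do not subtract it. Its look-back period need not match the follow-up year, since it only has to predict follow-up cost. Resample patients so that cost and QALY stay paired, refit the regression in each replicate, and use these replicates for the ICER, the plane and the acceptability curves. Report the unadjusted difference descriptively. Add a sentence saying that the mixed model of the effect evaluation does not supply the ICER numerator.

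The cost is a few sentences of text and one regression inside the planned bootstrap, with no new patients and no new data if the questionnaires are completed at baseline as implied. There are two caveats. GP consultations are reported separately for follow-up, so the covariate may not cover them and the gain may be smaller. A rule for missing baseline costs must also be written, because multiple imputation is planned only as a sensitivity analysis in the effect evaluation.

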## Methods: assignment of intervention

### Allocation and blinding

We will use Castor EDC for the online measurements and for randomisation of the participants [48]. Castor EDC uses a variable block randomisation method and randomly assigns participants to one of the two groups, the allocation ratio will be 1:1. The randomisation sequence is masked for study personnel. In order to balance the size of the intervention and usual care groups in each region, randomisation will be stratified according to regions (Amsterdam or Nijmegen). Patients will be included in either the intervention group or the usual care group based on the random allocation. The research assistant will give all patients a unique patient identification number, matching with the corresponding name to inform each participant about the allocation. All patients will be informed about the allocation by the research assistant by regular mail. Patients randomised to the psychosomatic therapy group will also be informed about the psychosomatic therapy by telephone by the research assistant and will receive a referral from their GP to one of the psychosomatic therapists participating in this study. If patients are randomised to the usual care group, they will be offered to receive psychosomatic therapy after completion of the study if still indicated. The research assistant will inform all GPs about the inclusion and allocation of their patients by regular mail or secure e-mail.

Since psychosomatic therapy is a face-to-face intervention, patients and therapists cannot be blinded to allocation. The data analysts will not be blinded to treatment assingments, as this would be unfeasible because they are also involved in data collection.

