#### Effect evaluation

##### Effectiveness of the intervention

Differences in the change scores between the intervention group and the control group on the primary and secondary outcomes will be analysed with multilevel (mixed-model) linear regression analyses taking all three measurements into account (baseline, and at 4 and 12 months). We will use a model with a random intercept and all other variables fixed.

A sensitivity analysis will be performed by replacing missing values by multiple imputation. *P* values < 0.05 are considered statistically significant.

Differences in the change scores between the cohort study group and both the intervention group and the control group on the primary, secondary and other study parameters will be analysed with multilevel (mixed-model) linear regression analyses, taking all three measurements into account. We will perform subgroup analyses for severity, duration and number of the symptoms and comorbidity to explore which patients are most likely to benefit from the intervention.

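### Incremental QALYs are area-under-the-curve differences that include baseline SF-6D utility, with no baseline adjustment named; this costs precision and lets part of any chance imbalance reach the ICER

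*Protocol article*

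**What the plan says.** All of the following is in the protocol article; no statistical analysis plan is shown.

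- **QALY construction** (Cost-effectiveness of the intervention): "Utility scores will be calculated through the SF-6D", and "QALYs will be calculated using the area-under-the-curve method, using the utility scores at baseline, 4 months and 12 months".
- **Comparison** (same section): "Differences in costs and QALYs per patient between the two treatment arms will be calculated, according to the ITT and the per-protocol principle". The per-protocol set keeps only those intervention patients who had four or more sessions.
- **Use of the differences** (same section): "Where relevant, incremental cost-effectiveness ratios (ICERs) will be calculated to reflect the extra costs per QALY gained", and "The bootstrap replications will be used to estimate 95% confidence intervals around cost and QALY differences". A cost-effectiveness plane and acceptability curves follow.
- **Guidance** (same section): the evaluation is to be done "in accordance with the Dutch guidelines for economic evaluation". The content of that guideline is not reproduced.
- **Clinical outcomes, for contrast** (Effectiveness of the intervention): change scores "will be analysed with multilevel (mixed-model) linear regression analyses taking all three measurements into account (baseline, and at 4 and 12 months").
- **Balance by design** (Allocation and blinding): allocation is 1:1 and "randomisation will be stratified according to regions (Amsterdam or Nijmegen"). No other stratification factor is named.

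**The concern.** Baseline utility is one of the three components of the QALY total, and it will usually also predict the two later utilities. If one arm starts with better utility by chance, part of that head start is counted as QALYs gained. Stratifying by region alone does not prevent this. Bootstrapping an unadjusted difference describes the resulting uncertainty but does not remove the imbalance.

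The mixed model for the clinical outcomes brings baseline into the analysis. As described, it cannot be fitted to a QALY total, which is a single number per patient with no baseline counterpart. So the article says how baseline is handled for the clinical outcomes and not for the quantity that forms the denominator of the ICER.

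Cost-effectiveness is a stated main aim, while the sample size rests on the PSFS. The QALY comparison has to make do with whatever precision it gets, so avoidable noise matters. The quoted sentence also covers the per-protocol comparison, which selects patients within one arm after randomisation.

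**Working it through.** **The plan's own figure.** The only sample size stated is for the PSFS (difference 1, SD 2, alpha 0.05 taken as two-sided, power 0.80, dropout 20%).

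- n = 2 × (1.960 + 0.842)² × 2² / 1² = 62.8, so 63 per arm.
- 63 / 0.80 = 78.75, so 79 per arm. This reproduces the stated figure. The check below uses 63 (completers) to 79 (randomised) per arm.

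**QALY weights.** The trapezoid rule with visits at 0, 4 and 12 months gives:

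- baseline: ½ × 4/12 = 1/6
- 4 months: ½ × 12/12 = 1/2
- 12 months: ½ × 8/12 = 1/3

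**Assumptions not in the documents.** SF-6D SD 0.08 to 0.15, equal at all visits; a common between-visit correlation ρ of 0.3 to 0.7.

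**Formulas.**

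- Expected carry-over of a baseline difference into the QALY difference: 1/6 + (5/6)ρ.
- QALY variance in units of SD²: (1/36 + 1/4 + 1/9) + (1 − 14/36)ρ = 0.389 + 0.611ρ.
- Variance after adjusting for baseline: that quantity minus the carry-over squared.
- Standard error (SE) ratio, adjusted to unadjusted: square root of the ratio of the two variances.

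| ρ | Carry-over | QALY variance | Adjusted variance | SE ratio |
|---|---|---|---|---|
| 0 | 0.167 | 0.389 | 0.361 | 0.96 |
| 0.3 | 0.417 | 0.572 | 0.399 | 0.84 |
| 0.5 | 0.583 | 0.694 | 0.354 | 0.71 |
| 0.7 | 0.750 | 0.817 | 0.254 | 0.56 |

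The ρ = 0 row shows the purely mechanical part.

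**Size of a chance imbalance.** The 95% range is ±1.96 × SD × √(2/n).

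- Smallest case (SD 0.08, n = 79): ±0.0249. With ρ = 0.3 the QALY shift is 0.417 × 0.0249 = ±0.010.
- Middle case (SD 0.10, n = 63): ±0.0349. With ρ = 0.5 the shift is 0.583 × 0.0349 = ±0.020. The SE falls from 0.0148 to 0.0106.
- Largest case (SD 0.15, n = 63): ±0.0524. With ρ = 0.7 the shift is 0.750 × 0.0524 = ±0.039.

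**Simulation.** 10,000 trials with no treatment effect, 63 per arm, SD 0.10 and ρ 0.5.

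- Both estimators average about zero (−0.0001 unadjusted, −0.0002 adjusted), so neither is biased over randomisations.
- Their SDs are 0.0149 and 0.0107, in line with the formulas.
- The slope of the estimate on the baseline difference is 0.57 unadjusted and −0.01 adjusted.

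**The case against.** The article never calls the difference raw or unadjusted. It says that differences will be calculated and bootstrapped, and regression-adjusted differences can be bootstrapped too. A condensed article may leave the covariates to an analysis plan, and it refers to a national guideline that is not shown. This stands. A reader might infer that the sponsor has decided against adjustment, but the documents show only that none is named.

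A reader might also infer that the ITT result is biased, or that a baseline imbalance passes whole into the ICER. Neither is supported. Under randomisation the unadjusted difference is correct on average, and its sampling variance, and so its bootstrap interval, already includes the variation due to chance imbalance. The carry-over is partial. Nor can the shift be said to equal or exceed the treatment effect, because the article states no expected QALY effect.

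The size depends on an SD and correlations from outside the documents. At ρ = 0.3 the gain is modest: the variance falls by 30% (1 − 0.399/0.572), against 69% at ρ = 0.7 (1 − 0.254/0.817).

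These limits do not dispose of the point. The section fixes the instrument, the area-under-the-curve method, the perspective, discounting, productivity valuation and the bootstrap, and leaves the estimator as a bare difference. An analyst who followed it literally would use the less efficient one. The randomisation argument also does not reach the per-protocol comparison.

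**Conclusion.** The point holds as one of efficiency and of conditional accuracy in the sample obtained. As written, incremental QALYs are differences in totals that contain baseline utility, with no adjustment named.

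- **ITT comparison:** no bias on average. A chance baseline imbalance carries over by 1/6 mechanically and by about 0.42 to 0.75 in total for ρ of 0.3 to 0.7. This amounts to about ±0.010 to ±0.039 QALY over the 95% range of imbalance, with SD 0.08 to 0.15 and 63 to 79 per arm. The SE would fall to about 0.84 to 0.56 of its unadjusted value.
- **Per-protocol comparison:** selection on attendance happens after randomisation and in one arm only, so baseline differences can be systematic. No size can be given from the documents.

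The weights and the mechanical sixth follow from the visit schedule alone. Every other magnitude rests on the assumed SD, the assumed correlations and equal variances across visits. The improvement is worth making before analysis. It does not show that the planned economic evaluation is invalid.

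**What to change.** State that incremental QALYs are estimated by regressing the QALY total on arm, baseline SF-6D utility and region (the stratification factor). Fit this regression within each bootstrap replicate, in both the ITT and the per-protocol analysis. Take the ICER, the cost-effectiveness plane and the acceptability curves from these adjusted differences. If an unseen analysis plan already says this, a sentence confirming it is enough.

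Adjust incremental costs for baseline costs only if the iMCQ and iPCQ are administered at baseline, which the text shown does not settle.

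In the per-protocol analysis the adjustment removes the part of the selection that runs through baseline utility, not selection on other characteristics, and the report should say so.

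The cost is a few lines of analysis code. Baseline utility is already needed for the QALY calculation, so there is no extra data collection and no change to the sample size.
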